### Study design

2.1.

An RCT will be conducted to study the effectiveness of a brief online psychoeducation programme called BLAME-LESS. The psychoeducation programme is an eHealth module with no active therapist involvement. Participants will be randomized into either the intervention group or the waiting-list control group. If allocated to the intervention group, participants will have direct access to the online intervention for two weeks after allocation. When a participant is assigned to the waiting-list control group, he or she has a two-week waiting period, after which the participant will have access to the intervention. Assessments take place after screening (T0), at baseline (T1), and two weeks after allocation (T2). Participants in the waiting-list group will also be assessed two weeks after they have gained access to the intervention (T3). Figure 1 provides an overview of the study design. The study protocol has been approved by the Medical Ethical Committee Oost-Nederland in the Netherlands (NL82795.091.22).

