When meeting the inclusion criteria, the participants will receive a letter with information about the intervention, study, and informed consent form. Parents (or legal guardians) from participants between the ages of 12 and 16 years will also receive a letter with information and will be asked for permission. Each participant can individually start with the intervention whenever they are ready. After inclusion and obtaining informed consent, participants will have one week to complete the baseline questionnaires (T1). Once they completed the baseline questionnaires, the randomization procedure will start. Participants will be randomly allocated to the intervention or waiting-list control groups. The Castor EDC will be used as a random-number generator. A 1:1 allocation ratio will be applied. We utilize block randomization with varying block sizes for this purpose, stratifying for the following variables: gender (boy, girl), type of trauma (physical violence, sexual abuse), and frequency of trauma (single occurrence, multiple occurrences) to ensure that the number of participants is well balanced across both treatment arms within each stratum. Randomization results will be communicated to the participants and their parents (or legal caretakers) via e-mail or phone calls. After the randomization procedure, participants will receive login codes on a website where they can engage in the online psychoeducation programme. The website is available through a login, which allows the research team to evaluate the parts of the website that have been visited and the time spent on the webpage. After two weeks, measurements will be taken (T2) for both groups. After T2, the participants referred to the waiting-list control group will receive access to the online psychoeducation programme. Two weeks after access, post-intervention measurements will be conducted (T3) for the waiting-list control group. Completing the questionnaires takes approximately 15–30 min per assessment. There are no costs incurred by the participants. Participants who dropout before the start of the intervention from the study will be replaced by new participants, with a maximum of 20% of all participants. Participants who dropout during the intervention will not be replaced.

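### The rule for replacing dropouts runs past randomisation and stays open longer in the waiting-list arm than in the intervention arm

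*Protocol article*

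**What the plan says.** All of this is in the protocol article.

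- **Replacement (Procedure).** "Participants who dropout before the start of the intervention from the study will be replaced by new participants". The number replaced is capped at one fifth of the sample. The next sentence sets the other side of the line: "Participants who dropout during the intervention will not be replaced".
- **Randomisation (Procedure).** "Once they completed the baseline questionnaires, the randomization procedure will start". The result is then passed to participants by e-mail or phone.
- **Access, intervention arm (Study design).** "participants will have direct access to the online intervention for two weeks after allocation".
- **Access, waiting-list arm.** Study design: "he or she has a two-week waiting period, after which the participant will have access to the intervention". Procedure agrees: "After T2, the participants referred to the waiting-list control group will receive access to the online psychoeducation programme".
- **Timing of use (Procedure).** "Each participant can individually start with the intervention whenever they are ready".
- **Primary comparison (Data analyses).** A group-by-time interaction on the SGATS, using T1 and T2 only, with 34 participants, 17 per arm.

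The article does not define the start of the intervention for the waiting-list arm. It does not say whether a replaced participant stays in the analysis.

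**The concern.** Replacing people lost between consent and randomisation does no harm, because no arm has been assigned. Replacing people after randomisation is different. They know their arm, and leaving may be a response to it. If the newcomer counts in the leaver's place, the groups compared at T2 are no longer the groups that were randomised.

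Here the cut-off is also tied to an event that falls at different times in the two arms. For the waiting list it falls after the primary endpoint. Whether a loss is made good by a new recruit or left as a loss therefore depends on allocation. What is at stake is how far a T2 difference can be credited to the programme, in a trial with only 17 people per arm.

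**Working it through.** **1. The cap.** 0.20 × 34 = 6.8, so at most 6 whole participants (7/34 = 20.6% would exceed it). This covers both arms together and includes losses before randomisation. If all six were replaced after randomisation, 34 + 6 = 40 people would be randomised for 34 kept.

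**2. The replacement window after allocation, by arm.**

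| If 'start' means | Intervention arm | Waiting-list arm |
|---|---|---|
| access granted | closes almost at allocation | open until after T2 |
| first use of the programme | open until first use | open until after T2 |

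Under either meaning the waiting-list window covers the whole T1 to T2 period. Take two people who leave on day 7 after allocation. One is in the intervention arm and opened the programme on day 2: not replaced. The other is on the waiting list: replaced.

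**3. What this could do to the estimate.** Assumptions, none from the article: 17 kept per arm; those replaced differ from those kept by D, in SDs of the T1 to T2 change; D is the same in both arms; those replaced are not analysed. With r replaced in an arm, the share removed is q = r/(17 + r). The shift relative to all randomised is D × (q in one arm − q in the other). Type I error is for a two-sided 5% t test on change scores (32 df, noncentrality = bias × √(17/2)).

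| Split | Difference in q | D = 0.3 | D = 0.5 | D = 1.0 | Type I error |
|---|---|---|---|---|---|
| 3/3 | 3/20 − 3/20 = 0 | 0 | 0 | 0 | 0.050 |
| 4/2 | 4/21 − 2/19 = 0.085 | 0.03 | 0.04 | 0.09 | 0.051, 0.052, 0.057 |
| 6/0 | 6/23 − 0 = 0.261 | 0.08 | 0.13 | 0.26 | 0.056, 0.066, 0.114 |

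Set against the article's planned d of 0.50 on the same scale, the 6/0 row is 16%, 26% and 52%. These are illustrations, not bounds. An even split is free of bias only if D is equal in both arms. With D = 1.0 in one and 0.3 in the other, a 3/3 split gives 0.15 × (1.0 − 0.3) = 0.105 SD.

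**4. Power, for the cost of the fix.** The article's 34 is reproduced by the repeated-measures interaction test with f = 0.25, m = 2 time points, α = 0.05 and an assumed T1–T2 correlation ρ = 0.5: λ = f² × N × m/(1 − ρ) = 0.0625 × 34 × 2/0.5 = 8.5, on 1 and 32 df. Power is 0.807 at N = 34 and 0.781 at N = 32. This takes f = 0.25 as the article enters it and does not judge its stated equivalence to d = 0.50.

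- 34 randomised, 20% lost, none replaced: about 27 to 28 remain, power 0.70 to 0.72.
- 40 randomised, 20% lost: 40 × 0.80 = 32 remain, power 0.781.
- To end with 34 after 20% loss: 34/0.80 = 42.5, so 43, or 44 for equal arms.

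**The case against.** The strongest reply has three parts.

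First, the start may be meant as the moment access is granted, or even allocation in both arms. On the access reading, hardly anyone in the intervention arm is replaceable after randomisation. That is fair, but it leaves the waiting-list window open to T2, so the difference between arms remains. On the allocation reading the difference disappears, but the article does not say this and its description of waiting-list access points the other way.

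Second, a true dropout gives no T2 score whether or not someone new is recruited, so selection comes from the loss and its handling. Analysis sets and missing-data methods may be in a fuller document. This stands in part: the article does not say that replaced people leave the analysis. But replacement, in its ordinary sense, lets the newcomer stand in for the leaver and removes the reason to pursue the leaver's T2. The rule itself is stated, so it is not an omission.

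Third, the numbers are small and some replacements will fall before randomisation. That stands, and it limits the size.

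A reader might infer three stronger things that the text does not support:

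- **That people who never log in are purged from the intervention arm, inflating the effect by a calculable factor.** The rule concerns dropout from the study. Someone who stays enrolled without using the programme is not plainly a dropout, and T2 is taken in both groups without reference to website use.
- **That the effect is overstated.** Waiting-list losses are replaced too, and the bias could go either way.
- **That replacements disturb the stratified block sequence.** Nothing says that a newcomer inherits the vacated slot.

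**Conclusion.** The concern holds in limited form. As written, the replacement rule continues after allocation is known and has a different reach in each arm. In the waiting-list arm it spans the entire primary comparison. That weakens the protection of randomisation without showing that the result will be biased.

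Any bias depends on how many leave each arm after randomisation and how they differ from those who stay, neither of which is known. With at most 6 replacements and assumed equal differences of 0.3 to 1.0 SD, the plausible range runs from nothing to about 0.26 SD. The upper end requires all six to come from one arm. The conclusion rests on the literal reading of the start of the intervention and on replaced participants not being analysed. The article states nothing that contradicts either.

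**What to change.** Replace the two sentences on replacement in Procedure with wording such as: *Participants who withdraw before randomisation may be replaced. No randomised participant is replaced; T2 is sought from everyone randomised, and all are analysed in the arm allocated.*

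The recruits already allowed under the 20% cap can be randomised as additional participants through the normal stratified sequence, up to 40 in total. Subject to the assumptions above, that recovers most of the power that a 20% loss would cost (0.781 against 0.70 to 0.72).

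The cost is small: two sentences, T2 requests to people who have stopped taking part but still agree to be asked, a possibly diluted effect estimate, and some missing T2 data to handle in the analysis. The change should be made before results are seen, because T2 scores that were never sought cannot be recovered later.

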### Intervention BLAME-LESS

2.5.

All participants will receive the online psychoeducation programme BLAME-LESS. This programme was developed in collaboration with trauma experts and adolescents who survived physical/sexual violence or sexual abuse. The programme was designed to educate about common defense responses that may occur during and after physical/sexual violence or sexual abuse. The main goal of the programme is to reduce the feelings of shame and/or guilt related to these responses. All aspects of the programme were created in collaboration with licensed developmental and clinical psychologists with extensive psycho-trauma expertise, adolescent experienced experts, visual artists, and web designers. The programme is offered via a website and consists of three modules (Table 1).

To ensure a comprehensive and effective learning experience, the BLAME-LESS programme integrates multimodal approaches. It incorporates a combination of different learning styles, including visual, auditory, and online reading activities. By catering to individuals with varying preferences, this approach provides a well-rounded learning experience that enhances engagement and knowledge retention.

The development of the BLAME-LESS programme also benefits from expert input. Guidance and information from professionals in relevant fields, such as psychologists, therapists, counsellors, and subject matter experts, are sought. Their expertise contributes to evidence-based knowledge, research findings, and best practices to ensure the programme’s effectiveness and credibility. In addition, personal testimonials play a crucial role in the BLAME-LESS programme. Real-life stories and experiences shared by adolescents who have experienced similar challenges or traumas are included. These personal narratives offer unique insights, relatability, and emotional connections for programme participants. By showcasing the journeys and perspectives of others who have faced similar situations, the programme fostered empathy, understanding, and a sense of community among its participants.

Some of the common elements addressed by Kooij et al. (2022) for evidence-based trauma therapy for children and adolescents are embedded in the online BLAME-LESS programme. Information about common defense responses and post-trauma reactions is provided (psychoeducation). In addition, the concept of cognitive shifting is used to influence or modify dysfunctional cognition by adding new information about the defense cascade.

The psychoeducational programme will take approximately 180 min to complete. Participants will receive a step-by-step guide on how to navigate the website and a checklist with all modules they can enrol in. It is advised that the participant will follow the psychoeducation programme while he/she is at home, and that they will have two weeks to watch, read, and listen to the entire programme on their own terms. They will be informed that the research team will track website use within the psychoeducation programme to monitor engagement. Participants will receive a login via email. The login code grants access to the website, which is provided in a restricted environment. Within this restricted environment, the research team ascertained which sections of the website had been viewed, and the duration the participant took for each section. The research team cannot track website use outside the psychoeducation programme environment. During the programme, a licensed psychologist can be contacted during working hours via e-mail and/or phone for their support and questioning. Contact information is provided through the information letter prior to the start of the study as part of the informed consent procedure. After the intervention, participants receive care as usual.

### Measurements

2.6.

Measures are administered at four time points: at screening (T0), at baseline (T1), two weeks after allocation to the intervention or waiting-list period (T2), and, only for the waiting-list participants, seven weeks after allocation to the intervention (T3). Questionnaires are distributed using Castor EDC and received by the participant via email.

An overview of the measurement instruments and time points is presented in Table 2.

**Table 2. T0002:** Measurement instruments and time points.

	Number of items	Maximum time to complete	Assessment time points
Screening			
Child Trauma Screening Questionnaire (CTSQ)	24 items	5 min	T0
Cognitive Emotion and Regulation Questionnaire (CERQ)	4 items	1 min	T0
Feelings of Shame and Guilt about Defensive Responses (VAS rating)	2 items	1 min	T0
Baseline			
Demographic information		NA	T1
Primary outcome			
Feelings of Shame and Guilt (SGATS)	9 items	5 min	T1, T2, T3*
Secondary outcomes			
Posttraumatic stress (KJTS)	25 items	10 min	T1, T2, T3*
Post-Traumatic Cognitions (CPTCI)	25 items	10 min	T1, T2, T3*
Motivations and Disclosure (TPEQ)	6 items	5 min	T1, T2, T3*
Anxiety and Depression (PROMIS)	16 items	5 min	T1, T2, T3*
Feelings of Shame and Guilt about Defensive Responses (VAS rating)	2 items	1 min	T1, T2, T3*
Other Questionnaires			
Feasibility Test	5 items	5 min	T2, T3**
Knowledge Test	6 items	1 min	T1/T2/T3*

Note. *Participants in the intervention group will not receive T3 measurements.

**For participants in the waitlist control group, this assessment will take place at T3.

#### Screening for traumatic experiences (CTSQ)

2.6.1.

The Child Trauma Screening Questionnaire (CTSQ; Kenardy et al., 2006) is a self-reported measure that contains a 14-item list of traumatic life events and a 10-item list to measure post-traumatic stress symptoms of re-experiencing and hyperarousal. Each life event can be answered with yes (scored as 1) or no (scored as 0). Scores >4 indicate positive screening for trauma symptoms. For screening, we will use only two items on the list of traumatic life events, namely items that refer to having experienced (sexual) violence and/or sexual assault (Items 1 and 2). The CTSQ has been shown to have good convergent validity (Kenardy et al., 2006). Internal consistency was reported, with a Cronbach’s alpha of .69.

#### Cognitive Emotion Regulation Questionnaire (CERQ)

2.6.2.

The Cognitive Emotion Regulation Questionnaire (CERQ; Garnefski et al., 2002) is a 36-item self-report questionnaire with five response categories: ‘(almost) never, sometimes, regularly, often, and (almost) always’. The items refer to what a person thinks when experiencing threatening or stressful events. The full questionnaire measured nine cognitive coping strategies. For screening, we will use only four items on the self-blame subscale (Items 1, 10, 19, and 28). Internal consistency of the self-blame subscale was alpha = .81 (high) for young adolescents (13–15 years) and .68 (medium) for older adolescents (16–18 years).

#### Demographics

2.6.3.

All children referred to child and adolescent psychiatry complete a comprehensive intake form and undergo an intake procedure. During this procedure, parents share demographic information to appropriately allocate care. In the present study, demographic information will be collected from medical files. The information will include age, sex, and school functioning.

#### Shame and Guilt After Trauma Scale (SGATS)

2.6.4.

The Shame and Guilt After Trauma Scale (SGATS; Aakvaag et al., 2016) measures trauma-related shame and guilt. The SGATS consists of nine items: four on trauma-related feelings of shame and five on trauma-related feelings of guilt (Aakvaag et al., 2016). Each question can be answered on a 3-point Likert scale (0 = no, 1 = yes, a little, 2 = yes, a lot). The minimum SGATS score is 0, and the maximum score is 18. The SGATS has a Cronbach’s alpha of 0.84 for feelings of shame and .87 for feelings of guilt. The SGATS was translated into Dutch using the five iterative stages described by Douglas and Craig (2007): translation, review, adjudication, pretesting, and documentation.

#### Child and Adolescent Trauma Screening (KJTS-NL)

2.6.5.

The Dutch version of the Child and Adolescent Trauma Screener (KJTS-NL; Kooij & Lindauer, 2019) is a questionnaire for children and adolescents that serves as a screening tool for PTSD symptoms (Sachser et al., 2017). The questionnaire consists of three parts. In the first part, adolescents are asked which major (traumatic) events they have experienced. In the second part, the severity of PTSD symptoms is measured with 20 items, rated on a 4-point Likert scale (range 1–4) and in the third part, the children and adolescents are asked to indicate (yes/no) whether the above-mentioned symptoms caused difficulties in certain daily activities. A total score below 15 suggests no (clinical) indication of the presence of a PTSD classification, a score between 15 and 20 suggests the possible presence of a clinical PTSD classification, and a score above 20 suggests an increased chance of the presence of a PTSD classification. Cronbach’s alpha for all components varies between .88 and .94 (Sachser et al., 2017). The results for the Dutch version of the KJTS are not yet available.

#### Child Post-Traumatic Cognitions Inventory (CPTCI)

2.6.6.

The Child Post-Traumatic Cognitions Inventory (CPTCI; Meiser-Stedman et al., 2009) is a self-report questionnaire that measures trauma-related cognition in children and adolescents. The questionnaire consists of two subscales (permanent and disturbing change subscale, CPTCI-PC; fragile person in a scary world subscale, CPTCI-SW) with a total of 25 items that can be answered on a four-point Likert scale, ranging from 1 (strongly disagree) to 4 (strongly agree). The English version of the CPTCI has been validated in children aged–6–18 years. The Dutch CPTCI has good reliability and validity (Diehle et al., 2015), high internal consistency (Cronbach’s alpha 0.86–0.93), and good convergent validity.

#### Treatment Program and Evaluation Questionnaire (TPEQ)

2.6.7.

The Treatment Program and Evaluation Questionnaire (TPEQ; Murphy et al., 2009) assesses readiness and motivation for trauma-focused treatment (Murphy et al., 2009). For the present study, we use four items (items 8 through 11 have been incorporated) from the TPEQ. Additionally, the two following items on Disclosure have been added to the questionnaire: ‘To what extent do you think: I will disclose everything during the treatment, even the things I feel ashamed of?’ and ‘To what extent do you think: I will disclose everything during the treatment, even the things I feel guilty about?’ All questions were answered on a 7-point Likert scale (ranging from 1 = strongly disagree to 7 = strongly agree). A higher score indicates greater willingness, motivation for treatment and readiness for disclosure in treatment.

#### Patient-Reported Outcomes Measurement Information System

2.6.8.

The Patient-Reported Outcomes Measurement Information System (PROMIS; Terwee et al., 2014) measures Anxiety and Depression symptoms. The lists consist of a dynamic set of item banks based on Computerized Adaptive Testing (CAT). Both questionnaires consist of 8 items. Each question can be answered as follows: never, almost never, sometimes, often, and very often. PROMIS is a short form of CAT, primarily utilized for research purposes. In the current study, the raw item scores will be summed, resulting in a PROMIS total score. Higher scores indicate more severe anxiety and/or depression symptoms. The calculated PROMIS total scores from different measurement points will be compared.

#### Feelings of shame and guilt: visual analog scale

2.6.9.

The participants rated guilt and shame on a by the authors developed 10-point visual analogue scale (VAS; 1 = no, not at all to 10 = yes, very much). Item 1: ‘Do you experience feelings of guilt regarding your own reactions during (or after) the stressful event, such as what you said and did, or perhaps what you did not say or do? Item 2: ‘Do you experience feelings of shame regarding your own reactions during (or after) the unpleasant event, such as what you said and did, or perhaps what you did not say or do?’

#### Feasibility

2.6.10.

We developed a short questionnaire with five questions that will be used to assess whether the BLAME-LESS programme intervention is attractive and easy for participants to use. We aim to assess whether the intervention was perceived as appealing (1) by the participants. We will explore how the participants experienced the tone of texts (2) and whether the animation resonated (3) with them. Furthermore, we will inquire whether the youth visited (4) all sections of the website and whether the information provided was clear (5). These open-ended questions are posed to the participant through an online form after the intervention’s completion. The information provided may be used to further adjust or optimize the intervention.

